#### Ambulatory assessment

The ambulatory assessment consists of daily questions about well-being, affect, sleep quality, the school situation, and social relationships that children and adolescents (30 items), the participating parent or caregiver (17 items), and, if teachers participate, a teacher (10 items), answer on their personal or a study smartphone via the app *movisensXS* [49] (see Fig. 3). The children’s and adolescents’ items are presented in written and audiovisual form, so that children who are not yet able to read confidently can have the items read aloud. Ambulatory assessment takes place every day between 5 and 9 o’clock in the evening from 2 weeks before discharge to 8 weeks after discharge and takes a maximum of 5 min per day. Teachers answer the items only on school days and have a larger time frame to respond to increase adherence by being more flexible. Children and adolescents, parents, and teachers are reminded of the daily survey by alarms and can postpone alarms three times. The data collected in the ambulatory assessment is evaluated individually on a weekly basis by summarizing all answers and preparing them graphically (see Fig. 4). The case-leading therapist can use this overview of the participants answers during the last week(s) as a basis for the next regular video call.

**Fig. 3 Fig3:**
[figure not shown]
Display of the app with one example item from the ambulatory assessment and with the identification figure PANDA

**Fig. 4 Fig4:**
[figure not shown]
Sample excerpt from the weekly graphical evaluation of the ambulatory assessment data for the therapist. o data point. 

missing. Color coding for school attendance (green = yes, yellow = partial, red = no, gray = no school day)

With the start of the ambulatory assessment, all participants receive a short technical briefing, in which the app *movisensXS* [49] is installed on the participant’s Android smartphone or a study smartphone. When using their own smartphones, the participants can be reimbursed for data used for the daily surveys. After installation of the app *movisensXS* [49], all technical components of the study are briefly explained and tested: (1) the app *movisensXS* [49] with messenger function, (2) the video phone program VidyoConnect [51], (3) the university hospital’s own cloud service for the pseudonymized worksheets of the weekly goals and other therapy materials, and (4) the online platform SoSci Survey [50] for post- and follow-up surveys. Despite the intuitive and simple handling of all components, all participants receive written, illustrated instructions. For further questions or in case of technical difficulties, the study contact details (e-mail address and telephone number) are also included in the instruction.

#### Instruments

The instruments used in DigiPuR (see Table 1) are chosen to cover the five domains (symptoms, functioning, consumer perspectives, environments, systems) of the comprehensive conceptual model of outcomes of mental health care for children and adolescents [46]. The instruments and scales used in the pre-post-follow-up assessment and the ambulatory assessment are briefly described in the following, sorted according to the five domains. Item formulations were adapted where necessary so that they are understandable and suitable for both children and adolescents. Items are only presented if their content is relevant to the respective group (e.g. items on satisfaction with the program for video calls only when it was used). Primary outcomes are number of readmissions, satisfaction with treatment, health-related quality of life, and symptom severity; all others are secondary outcomes (see Table 1). As there is a great heterogeneity of diagnoses in the patient sample, the evaluation aims to assess the reintegration phase and the well-being of patients globally and across disorders. General constructs relevant to different disorders were selected and instruments were used for comparability across the age range.

**Table 1 Tab1:** Overview of assessed outcomes, assigned domains, instruments, and raters at the different study time points

Outcome	Domain [46]	Instrument or scale	Rater	Study period				
				Enrollment	Allocation	Post-allocation		
				Admission	Ambulatory assessment (2 weeks before discharge until 8 weeks after)	Pre (discharge)	Post (8 weeks after discharge)	Follow-up (24 and 36 weeks after discharge)
Symptom severity	Symptoms	DISYPS-III SCREEN [52]	CA, P*, T*	x		x	x	x
Stress vulnerability and coping strategies	Symptoms (part 1), functioning (part 2)	Adapted from SSKJ-3-8R (parts 1 and 2) [53]	CA	x		x	x	x
Self-efficacy	Functioning	WIRKSCHUL [54], WIRKSOZ [54], WIRKLEHR [54], WIRKELTERN (self-development)	CA, P, T	x		x	x	x
Health-related quality of life	Consumer perspectives, environment	KIDSCREEN-27 [55]	CA, P*	x		x	x	x
Occupational well-being	Environment	Emotional exhaustion [56], enthusiasm for teaching [56]	T			x	x	x
Satisfaction with treatment	Consumer perspectives	Adapted from FBB [57]	CA, P, T, TH				x	
Satisfaction with technical components	Consumer perspectives	SUS [58], self-development	CA, P, T, TH				x	
Expectation of change	Consumer perspectives	Adapted from patient’s expectation of change [59]	CA, P			x		
Parental stress	Consumer perspectives, environment	EBI [60]	P	x		x	x	x
Parental strain	Consumer perspectives, environment	BSCL [61]	P	x				
Competence self-concept in dealing with students	Environment	Competence self-concept in dealing with students [62]	T			x	x	x
Professional competence in dealing with students with mental disorders	Environment	Self-development, Selection of different items from [54, 56, 63–66]	T			x	x	x
Number readmissions, and general information	All domains	Hospital documentation, self-development	P, T, TH	x		x	x	x
General well-being	Symptoms	Self-development	CA, P, T, P*, T*		x			
Affect	Symptoms	Affect [67]	CA, P		x			
Sleep quality	Symptoms	Sleep quality [67]	CA		x			
School absenteeism	Functioning	Self-development	CA		x			
School day	Functioning	Academic success [68]; adapted from KIDSCREEN-27 [55]	CA, T*		x			
Relationship with peers, parents and teachers	Consumer perspectives, environment	Peer relatedness [69], adapted from KIDSCREEN-27 [55]	CA, P*, T*		x			
Support from the hospital	Systems	Self-development	T		x			

*Note*. All items presented in German. *CA* children and adolescents, *P* parent, *T* teacher, *TH* therapist. *Assessed regarding the child or adolescent

##### DISYPS-III SCREEN (Diagnostic System for Mental Disorders according to ICD-10 and DSM-5 for Children and Adolescents - III Screening questionnaire)

The DISYPS-III SCREEN [52] contains five superordinate scales for overall symptomatology, internalizing and externalizing behaviors, contact behavior, and functional impairment and distress, as well as seven disorder-specific subscales. In the present study, overall symptomatology is utilized to evaluate the symptom severity from the perspective of the patients (self-evaluation questionnaire SBB; 55 items), parents, and teachers (external evaluation questionnaire FBB; 55 items). In addition to the superordinate scales, the corresponding disorder-specific subscales are analyzed. The manual reports satisfying psychometric properties (internal consistency of the overall symptomatology: Cronbach’s *α* = .91 for SBB and *α* = .92 for FBB, disorder-specific subscales between *α* = .49 and *α* = .85).

##### Questionnaire based on the SSKJ 3-8R (Questionnaire for the Survey of Stress and Stress Coping in Childhood and Adolescence – Revision)

The SSKJ 3-8R [53] contains three parts: (1) stress vulnerability, (2) stress coping strategies, and (3) stress symptomatology and well-being. In the present study, a self-developed questionnaire based on items of the SSKJ 3-8R measures children and adolescents’ (1) stress vulnerability with seven items on seven different situations and (2) stress coping strategies with 30 items on five scales. Deviating from the original version, the items on stress coping strategies are answered only in relation to one situation, which the children and adolescents choose beforehand from the previous stressful seven situations. The manual reports for the original version satisfying psychometric properties (internal consistencies between *α* = .67 and *α* = .89; retest reliabilities between *r*_*tt*_ = .61 and *r*_*tt*_ = .82).

##### Self-efficacy scales

Self-efficacy in dealing with social demands in children and adolescents is assessed via the scale WIRKSOZ [54] with eight items (internal consistency *α* = .60). School-related self-efficacy of children and adolescents is assessed via the scale WIRKSCHUL [54] with seven items (internal consistency ranges from *α* = .70 to *α* = .73). For the assessment of teachers’ self-efficacy in relation to students with mental disorders and in relation to the student to be reintegrated, 5 of the total 10 items of the Teacher Self-Efficacy scale, WIRKLEHR [54], were selected for the present study and adapted thematically in each case. Internal consistency of the original WIRKLEHR scale ranges from *α* = .76 to *α* = .81. To assess parents’ social self-efficacy in dealing with their child, the first 8 of the total of 10 items from the WIRKLEHR scale were thematically adapted and combined to form the WIRKELTERN scale.

##### KIDSCREEN-27

The KIDSCREEN-27 [55] measures the health-related quality of life of children and adolescents with 27 items on five dimensions (physical well-being, psychological well-being, relationship with parents and autonomy, peers and social support, school environment). In the present study, health-related quality of life is assessed from the perspective of both the child or adolescent and the participating parent. The manual reports satisfying psychometric properties (internal consistency between *α* = .80 and *α* = .84; intraclass correlation coefficients for retest reliability between .61 and .74).

##### Emotional exhaustion and enthusiasm for teaching

The scales emotional exhaustion (4 items; internal consistency between *α* = .74 and *α* = .82) [56] and enthusiasm for teaching (3 items, number 4, 5 and 6 selected; internal consistency between *α* = .69 and *α* = .81) [56] are used in the present study to assess teachers’ occupational well-being (see also [70]).

##### Questionnaire based on the FBB (Questionnaire for the Assessment of Treatment)

The FBB [57] is a German questionnaire used for therapy evaluation and quality assurance of psychotherapeutic and psychiatric treatments of children, adolescents, and families in research and practice. In addition to overall satisfaction with the treatment, outcome quality (treatment success) and process quality (course of treatment) are measured as subjective assessments of treatment. In the present study, four self-developed versions (patients: 20 items, parents: 21 items, therapists: 27 items, teachers: 14 items) adapted from items of the FBB are used, in which the word “treatment” was specified by “aftercare treatment”. In the patient version, item number 13 on video recordings was deleted because there are no video recordings in the present study. Item number 5 was added to the therapist version, asking about relationships in school in addition to relationships in the family. In addition, a version for teachers was designed from 14 items of the parent version of the FBB. The manual reports for the original versions satisfying psychometric properties (internal consistency between *α* = .63 and *α* = .94 for all raters; retest reliabilities for patients and parents ranged from *r*_*tt*_ = .36 to *r*_*tt*_ = .79).

##### SUS (System Usability Scale)

Satisfaction with the technical components is assessed among children and adolescents (23 items), parents (23 items), teachers (22 items), and therapists (15 items; no items regarding the app). The 10 items of the widely used technology-independent questionnaire SUS [58] were thematically adapted to the aftercare app and the program for the video calls, both used in the present study (e.g., “I thought the aftercare app was easy to use”). A study of the factor structure of the SUS reported an internal consistency of *α* = .92 [71]. Further self-developed items asked about things that did not work (all raters), preferences in aftercare (children and adolescents, parents, therapists), and the usefulness and inclusion of the weekly graphic evaluation (therapists).

##### Expectation of change

Patients’ and parents’ expectation of change regarding the aftercare is assessed as a covariate with 4 thematically adapted items (e.g., “I think that through DigiPuR I will cope better with my daily life”) from the scale *Patient’s expectation of change* of the questionnaire for measuring common factors in psychotherapy (FERT; factorial reliability of the original scale with 8 items ρϲ = .94) [59].

##### EBI (Eltern-Belastungs-Inventar)

The EBI [60] is the German version of the Parenting Stress Index [72] and measures parental stress with 48 items. In the present study, parental stress is assessed by means of the total scale and the twelve subscales. The manual reports satisfying psychometric properties (internal consistency of the total score *α* = .95 and of the subscales between *α* = .61 and *α* = .83; retest reliability *r*_*tt*_ = .87 for total scale).

##### BSCL (Brief Symptom Checklist)

The BSCL [61] contains 53 items to assess psychological strain in self-judgment on three global indices and nine scales. In the present study, the BSCL is used as a covariate to assess psychological strain in parents. The manual reports satisfying psychometric properties (internal consistency for the total score *α* = .97 and for all scales *α* ≥.72; retest reliability *r*_*tt*_ = .87 for the total score and *r*_*tt*_ ≥.64 for all scales).

##### Competence self-concept in dealing with students

Teachers’ competence self-concept in dealing with students is assessed with four items [62]. A recent study reported an internal consistency of *α* = .77 [73].

##### Professional competence in dealing with students with mental disorders

The professional competence of teachers in dealing with students with mental disorders is exploratively examined. Orientated on the framework model of teachers’ professional competence [74], seven competence facets relevant to the present study (professional, pedagogical-psychological, organizational, and counseling knowledge as well as motivational orientations, self-regulation, and beliefs/values attitudes) were thematically adapted: knowledge about mental disorders (5 items), knowledge about dealing with the student with mental disorders (11 items), knowledge about mental emergencies (3 items), knowledge about counseling of affected persons (8 items), motivation and self-efficacy (13 items), self-regulation (8 items), and responsibility and relationship with students with mental disorders (13 items). For this purpose, items of different studies from the field of Mental Health Literacy [63–65] and from teacher survey studies [54, 56, 66] were selected, thematically adapted where necessary as well as own items were developed.

##### Hospital documentation on general information

General and professional information about participants is obtained from hospital documentation and anamnesis forms for families (e.g., diagnoses, medications, level of psychosocial functioning, duration of treatment) and is collected from teachers at study inclusion (e.g., years in the profession, type of school, teaching load, professional contact with students with mental disorders). Further information for a health economic evaluation is obtained by analyzing controlling data (e.g., percentage of readmissions; travel times; contact via messenger) and the therapist’s documentation (e.g., worksheets on weekly goals; missed appointments; cooperation with support systems; implementation of therapy suggestions).

##### Ambulatory assessment

Ambulatory assessment items contain information on children and adolescents’ general well-being (1 item; self-development), affect (12 items) [67], sleep quality (2 items) [67], school absenteeism (2 items; self-development), school day (4 items; three items to perceived success at school [68] and one item adapted from the KIDSCREEN-27 [55]), and relationship with peers (4 items) [69], parents (4 items; adapted from [69]), and teachers (1 item; adapted from the KIDSCREEN-27 [55]). Parents make corresponding statements in the ambulatory assessment about their own general well-being (1 item; self-development) and affect (12 items) [67], as well as about their child’s general well-being (1 item; self-development) and their relationship with the child (3 items; adapted from [69]). Teachers make statements in the ambulatory assessment about the support they receive from the hospital (1 item; self-development) and about contact with the student being reintegrated (filter question). If there was contact with the student, teachers make statements about their general well-being, their well-being in their role as a teacher, and the well-being of the student (1 item each; self-development) as well as about the teacher-student relationship (1 item; adapted from the KIDSCREEN-27 [55]) and the school day (4 items; three items adapted from [68] to perceived success of the child at school and one item adapted from the KIDSCREEN-27 [55]). Additional comments or observations about the day can be indicated by parents and teachers in an open response format at the end of each assessment.

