#### Statistical analyses

All analyses are conducted using R software [48]. All outcome variables measured pre-post-follow-up will be analyzed with separate mixed ANOVAs. Preprocessing of the data and calculation of individual values will be done according to the respective manual. Predictors will be group (intervention vs. control) and time point, as well as their interaction. Treatment success would be demonstrated by a significant interaction effect of group and time point, being shown, through adequate post hoc test, to be due to different time-effects in the two groups. We do not necessarily expect the intervention group to improve in absolute values over time, as measures can decline after discharge. Rather, we expect the intervention group to develop better over time than the control group, meaning that even a stabilization of values might be considered a success. This better development in the intervention group than in the control group should be evident in the information provided by patients themselves, as well as by parents and teachers.

The successful reintegration into daily (school) life is conceptualized besides the pre-post-follow-up assessment by the data collected in the ambulatory assessment. All ambulatory assessment data will be analyzed with multi-level models [78]. We expect the reports from patients, parents, and teachers in the intervention group to show a significantly more positive trend over time in terms of their general well-being, affect, sleep quality, school absenteeism, situation in class, and the relationship with parents, peers, and teachers, than those in the control group. Statistically, these effects are shown by a significant interaction of the within-person time trends of these reports with group membership, being due to participants in the intervention group developing better (or less bad) than participants in the control group. Variables will be adequately centered, and appropriate fixed and random effects will be included in the models.

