Few missing data are expected due to ongoing monitoring. Missing data from single items of the standardized questionnaires will be handled appropriately according to the instructions in the manual. In case of complete questionnaires missing for a participant, this participant will be excluded from all ANOVAs containing this questionnaire. As multi-level models can handle missing data quite well, if they are at least missing at random, no data will be excluded from those analyses. However, appropriate variables (e.g., age, symptom severity) will be used to investigate if the missingness structure can be explained by them, rendering it to be not at random. In that case, those variables will be included in the according models to account for this non-randomness.

Due to the confidentiality of patient health data, data sets cannot be made publicly available. Access is only granted to study management who supervise data management and have a duty of confidentiality.

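### Eight of the ten daily teacher items are asked only on days with student contact, so the teacher-rated group-by-time comparison can be biased if attendance diverges between the arms

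*Protocol article*

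**What the plan says.** **Data collection.** In the Protocol article (Instruments, Ambulatory assessment), teachers answer one item on hospital support and one on whether they had contact with the pupil. The remaining items are conditional: "If there was contact with the student, teachers make statements about their general well-being, their well-being in their role as a teacher", followed by the pupil's well-being, the teacher-student relationship and four items on the school day. The earlier Ambulatory assessment paragraph under Evaluation gives a total of ten teacher items and adds: "Teachers answer the items only on school days and have a larger time frame to respond". Absenteeism is reported daily by the children themselves, with two items.

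**Analysis.** The Statistical analyses section sends all daily data to multi-level models. It expects patients, parents and teachers in the intervention arm to report the better trend in "general well-being, affect, sleep quality, school absenteeism, situation in class, and the relationship with parents, peers, and teachers". The evidence is to be a significant interaction of within-person time trend and group.

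**Missing data.** The same section states: "As multi-level models can handle missing data quite well, if they are at least missing at random, no data will be excluded". Variables such as age and symptom severity are to be examined as explanations of missingness and, if they explain it, added to the model. Nothing is said about items that the filter skips.

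**Status.** The Hypotheses and Instruments sections make the ambulatory outcomes secondary, and teacher participation is optional.

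**The concern.** Whether a teacher rating exists on a given day depends on contact, and contact depends largely on the pupil being in school. School absenteeism is itself an outcome that the intervention is expected to improve. The set of rated days is therefore fixed after randomisation, by something that treatment may change.

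Suppose the aftercare increasingly brings pupils to school on their harder days. Those days add low ratings in the intervention arm, while the corresponding control days produce none. The two arms are then compared on differently selected days, and the selection changes over time, which is the dimension that the success criterion tests. A programme that helps pupils return could look neutral or harmful on teacher reports.

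Covariates such as age or symptom severity do not remove this, because the selection works through the pupil's state on the day. Same-day attendance would help little as a covariate, since a pupil whom the teacher met will usually have been in school. For the pupil-related items there is also no missing value to recover: a school day that was not attended has no rating.

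The two items on the teacher's own well-being are a separate matter. They need no contact, yet they are lost on every day without it, and no later analysis can restore them.

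**Working it through.** **1. Item count (from the document).** 1 support + 1 filter + 3 well-being (own general, own as teacher, pupil) + 1 relationship + 4 school day = 10, which agrees with the stated total. Behind the filter: 3 + 1 + 4 = 8. Of these eight, two concern the teacher alone.

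**2. Selection effect on the mean level.** Let the pupil's daily state be standard normal, p the share of days with contact, and ρ the correlation between state and attendance. The mean state on contact days is shifted by ρ·φ(c)/p, with c = z(1−p).
- φ(c)/p is 0.644 at p = 0.60 and 0.350 at p = 0.80, a difference of 0.294.
- With no true difference, the apparent gap at 60% against 80% is −0.088 (ρ = 0.3), −0.147 (ρ = 0.5) or −0.206 SD (ρ = 0.7), and 0 at ρ = 0.

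This is a gap in level. If attendance is constant over time within each arm, the shift is the same at every time point and adds nothing to the planned interaction. The interaction has to be examined directly.

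**3. Selection effect on the group-by-time interaction (simulation).** The document gives no attendance rates or correlations, so all of the following are assumptions:
- 40 school days (8 weeks × 5), with time t running from 0 to 1.
- State = pupil effect + daily effect, each with variance 0.5, plus a true benefit δ·t in the intervention arm.
- Attendance 60% in control; 60% + 25 percentage points × t in the intervention arm. Contact is equated with attendance.
- Attendance correlates with the pupil effect (between) and with the daily effect (day-level).
- Random-intercept model of group, time and their interaction. Bias was estimated with 20,000 pupils per arm (standard error 0.004 to 0.005) and error rates with 1,500 trials of 25 per arm, two-sided 5%.

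| Day-level ρ | Between ρ | Intervention attendance | True δ (SD) | Contact-day estimate | All-day estimate | Significantly worse |
|---|---|---|---|---|---|---|
| 0 | 0 | 60→85% | 0 | 0.000 | −0.002 | 2.9% |
| 0 | 0.7 | 60→85% | 0 | −0.005 | −0.001 | 2.6% |
| 0.5 | 0 | 60→85% | 0 | −0.122 | +0.002 | 17.0% |
| 0.5 | 0.5 | 60→85% | 0 | −0.127 | +0.001 | 15.9% |
| 0.7 | 0.7 | 60→85% | 0 | −0.175 | 0.000 | 33.0% |
| 0.5 | 0.5 | 60→85% | +0.10 | −0.023 | +0.105 | 4.9% |
| 0.7 | 0.7 | 60→85% | +0.10 | −0.085 | +0.093 | 8.9% |
| 0.7 | 0.7 | 60→85% | +0.20 | +0.027 | +0.201 | 1.7% |
| 0.7 | 0.7 | 60→85% | +0.30 | +0.121 | +0.303 | 0.1% |
| 0.7 | 0.7 | 60% constant | +0.20 | +0.201 | +0.195 | 0.1% |

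The nominal rate for "significantly worse" is 2.5%. Bias appears only when attendance diverges between arms over time and depends on the day-to-day state. If either condition is absent, it is about zero.

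**The case against.** **The filter is sensible for most items.** A teacher who did not meet the pupil cannot rate the pupil's school day. This stands for the six pupil-related items, but not for the two on the teacher's own well-being.

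**The handling may be set out in an analysis plan that is not shown.** This stands in part: how days without contact enter the model is commonly left to such a plan, and the article's list of variables for examining missingness is open. But the filter, the success criterion and the reliance on missing at random are fixed in the article, and a later plan cannot recover items never asked.

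**The model absorbs part of the problem.** It does. With dependence only on stable differences between pupils, the simulated bias was −0.005 SD.

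**The stakes are limited.** The outcomes are secondary and teachers optional. The children's and parents' daily reports carry no such filter. If attendance improves, the bias runs against the intervention, so it would not create a false claim of success.

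Several stronger readings are tempting, and the document does not support them:
- A reader might take the level gaps in step 2 as the bias in the planned test. The plan tests a trend interaction, to which constant attendance adds nothing.
- A reader might infer that the teacher results will be reversed. That needs assumptions about attendance for which the document gives no figures, and a true benefit of +0.20 SD or more kept its sign in every case simulated.
- A reader might equate contact with attendance. A teacher may not meet a pupil who is at school.
- A reader might say that all teacher ratings are filtered, or that the plan explicitly treats skipped items as ordinary missing data. The support item is asked regardless, and the text is silent on skipped items.

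**Conclusion.** The point holds as a conditional risk to secondary, teacher-reported outcomes. The article makes eight of ten teacher items depend on contact, expects gains in both attendance and teacher-reported trends, and names no safeguard that addresses selection of days after randomisation.

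Under attendance rising from 60% to 85% against a constant 60%, with day-level correlation 0.5 to 0.7, the interaction is biased by about −0.12 to −0.18 SD. At 25 per arm and no true effect on state, the intervention would appear significantly worse in about 16 to 33% of trials instead of 2.5%. A true benefit of 0.10 SD would be estimated as −0.02 to −0.09 SD.

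These sizes rest on assumed attendance and correlations, on equating contact with attendance, on independent daily effects and on a random-intercept model; the article leaves its random effects open. The primary outcomes are untouched. What changes is how far the contact-day teacher models can support a conclusion on their own, in either direction.

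**What to change.** 1. For participants still to be assessed, ask the teacher's two own well-being items on every school day, before the contact filter.
2. Report, by arm and over time, the share of school days with teacher contact and the child-reported attendance. Read these before the teacher ratings.
3. Label the contact-day models of pupil well-being, relationship and school day as conditional on contact, and draw no stand-alone conclusion of benefit or harm from them.
4. A composite or two-part analysis of attendance and rating may be added as a sensitivity analysis only, with both parts shown. It should not replace the main analysis. Scoring each missed day as the lowest rating, for instance, would count every absence, including ordinary physical illness, as the worst relationship or well-being, and would largely duplicate the attendance outcome.

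**Cost.** Two app items are moved, and a little more analysis is done on data already collected. Recruitment began in March 2021 and the article describes the trial as ongoing, so early and late participants would differ in how these two items are filtered. That must be noted in the report. Steps 2 to 4 can be applied to all participants.
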